## Abstract

**Background:**

Knee osteoarthritis is a major cause of pain and functional limitation. Complementary and alternative medical approaches have been employed to relieve symptoms and to avoid the side effects of conventional medication. Moxibustion has been widely used to treat patients with knee osteoarthritis. Our past researches suggested heat-sensitive moxibustion might be superior to the conventional moxibustion. Our objective is to investigate the effectiveness of heat-sensitive moxibustion compared with conventional moxibustion or conventional drug treatment.

**Methods:**

This study consists of a multi-centre (four centers in China), randomised, controlled trial with three parallel arms (A: heat-sensitive moxibustion; B: conventional moxibustion; C: conventional drug group). The moxibustion locations are different from A and B. Group A selects heat-sensitization acupoint from the region consisting of Yin Lingquan(SP9), Yang Lingquan(GB34), Liang Qiu(ST34), and Xue Hai (SP10). Meanwhile, fixed acupoints are used in group B, that is Xi Yan (EX-LE5) and He Ding (EX-LE2). The conventional drug group treats with intra-articular Sodium Hyaluronate injection. The outcome measures above will be assessed before the treatment, the 30 days of the last moxibustion session and 6 months after the last moxibustion session.

**Discussion:**

This trial will utilize high quality trial methodologies in accordance with CONSORT guidelines. It will provide evidence for the effectiveness of moxibustion as a treatment for moderate and severe knee osteoarthritis. Moreover, the result will clarify the rules of heat-sensitive moxibustion location to improve the therapeutic effect with suspended moxibustion, and propose a new concept and a new theory of moxibustion to guide clinical practices.

**Trial Registration:**

The trial is registered at Controlled Clinical Trials: ChiCTR-TRC-00000600.

## Background

Osteoarthritis (OA) is the most common form of arthritis [1] and the leading cause of disability among older adults [2,3]. As one part of weight-bearing peripheral and axial joints, knee is the most commonly affected by osteoarthritis [4]. Among adults aged 30 years, symptomatic knee OA occurs in 6% and symptomatic hip OA in about 3%[4].Knee osteoarthritis (KOA) is associated with symptoms of pain and functional disability. Physical disability arising from pain and loss of functional capacity reduces the quality of life and increases the risk of further morbidity and mortality [5]. The prevalence, disability, and associated costs of KOA are expected to steadily increase over the next 25 years because of aging in the population [6]. After adjusting for age, sex, and comorbidity, KOA is responsible for a higher percentage of disability than any other medical condition for the following activities: stair climbing, walking a mile, and housekeeping.

The underlying disease processes of KOA involve cartilage degeneration, proliferation and remodeling of subchondral bone structure. Recently there is no cure for KOA [7]. Therefore, the treatment of KOA is primarily focused on managing the condition by minimizing morbidity. The current conventional treatment of KOA symptoms and analgesics, such as NSAIDS, glucosamine, topical analgesics, intra-articular (Sodium Hyaluronate, Synvisc) and surgical treatment[8,9]. Substantial numbers of patients with KOA are not satisfied with conventional drug treatment and repeatedly experience side effects [10,11]. As a result, a large number of patients with KOA are turning to complementary and alternative treatments. Non-pharmacological treatments such as acupuncture are therefore attractive. Acupuncture is often used for KOA. For example, it is gaining popularity among KOA patients in the US and about 1 million consumers utilize acupuncture annually which has musculoskeletal disorders [12].

Acupuncture is a safe treatment that has a low risk for serious side effects. Moxibustion is a traditional Chinese method of acupuncture treatment, which utilizes the heat generated by burning Moxa (it is also called Mugwort or Moxa) to stimulate the acupuncture points. The technique consists of lighting a moxa stick and bringing it close to the skin until it produces hyperaemia due to local vasodilatation. The intensity of moxibustion is just below the individual tolerability threshold. Moxibustion has anti-inflammatory or immunomodulatory effects against chronic inflammatory conditions in humans [13]. Moreover, the heat of moxa treatment improves microcirculation in the knee. Therefore, these Arthritis substances may be reduced and weakened by moxibustion. Then Elimination of swelling and pain relief also may be achieved. Especially for swell type KOA, which derived from surrounding tissues strain, moxibustion may get a better effect. Further deterioration of cartilage is set back, as a result of pathological chain of KOA is cut in treatment of moxibustion. That is to say, moxibustion does not make osteophyte disappeared in short treatment, but its therapeutic effects relieve the main symptoms, and minimizing morbidity of new osteophyte by avoiding pathological product of stimulus and mechanical structural imbalance.

Although firm evidence has not been established, the results of some systematic review and meta-analysis suggest that acupuncture and moxibustion may effective in the treatment of KOA [14-16].Such as the latest meta-analysis concluded that sham-controlled trials showed clinically irrelevant short-term benefits of acupuncture for treating knee osteoarthritis. Waiting list controlled trials suggested clinically relevant benefits, some of which may be due to placebo or expectation effects [16]. However, these reviews do not confirm the efficacy of acupuncture and moxibustion. This may be because all relevant RCTs were limited by methodological defects, including inappropriate sample size, variability of acupuncture and sham protocols, and missing information. Therefore, rigorous high-quality randomised controlled trials are needed.

Thinking about moxibustion itself, the selection of location for manipulating Moxa plays an important role in obtaining good effects [17]. In our opinion, the nature of acupoint is not location , but status. In the human being there are two functional states, sensitization state and rest state. When the human body has disease, acupoints on the body surface may be sensitized with various types of sensitization, and acupoint heat-sensitization is a type of acupoint sensitization. The sensitized acupoints show acupoint-specific "small stimulation inducing large response" for external relative stimulation. The Inner Canon of Huangdi or Yellow Emperor's Inner Canon is an ancient Chinese medical text that has been treated as the fundamental doctrinal source for Chinese medicine for more than two millennia and until today. According with its core viewpoint and theory, acupoint is described and understood with the state , which is certain area of the skin in the course of diseases. Among the changes, sensitized status is the common one, described that acupoints on the body surface may be sensitized with various types of sensitization. This sensitized acupoint is not only the pathological phenomenon reflecting the diseases but also stimulating location with acupuncture and moxibustion. Acupoint heat-sensitization is a type of acupoint sensitization.

Our research term found that the heat-sensitized phenomenon was a new type of acupoint sensitized features in pathological state [18-20]. We applicated the acupoint heat-sensitization phenomenon and rule in the past twenty years. The past experiential evidences in our research indicated that the functional state might jump from the rest state to the heat-sensitized state suffering from diseases. Its characteristic was thought that these special acupoints might produce heat response and farther warm sensation, as a result of stimulation of moxibustion heat. If we can search out these heat-sensitized acupoints associating with pathological state, good effect will be achieved. Therefore, selecting the heat-sensitized acupoint may obtain therapeutic effect far better than acupuncture and moxibustion at acupoints of routine rest state. We carried our many clinical trials to test and verify the efficacy heat-sensitized acupoint, such as myofascial pain syndrome [21], lumbar disc herniation[22], pressure sores[23] and KOA[24]. The result of clinical trials almost suggested superiority effect of heat-sensitized acupoint and encouraged us to proceed.

With these constraints, we planned a rigorous multi-centre randomised controlled trial with a large sample size.

## Method/design

### Objective

The aim of this study is to investigate the effectiveness of heat-sensitive moxibustion compared with conventional moxibustion or conventional drug treatment (intra-articular Sodium Hyaluronate injection) in patients with moderate to severe KOA in China.

### Outcome

Ministry of Health of the People's Republic of China (MHPRC) has proposed a series of criteria to define patient response in the context of clinical trials of KOA, known as the guiding principle of clinical research on new drugs (GPCRND) [25]. According to these criteria, a patient with KOA is assessed including pain, the relation between activity and pain, function impairment, and special exams (Table 1). This scoring system was previously validated. The degree of KOA is divided into three level: mild- < 5 score;moderate-5 ~ 9 score; severe-> 9 score.

**Table 1 T1:** List of GPCRND-KOA

Item	Grade/Classification	Score
Pain or discomfort in night when lying in bed	No	0
	Pain in activity or some position	1
	Pain in non-activity	2
Morning stiffness or pain worse when getting out of bed	No	0
	< 30 minutes	1
	≥ 30 minutes	2
Pain or discomfort in walk	No	0
	After walking in some distance	1
	Pain at beginning of walk or worse	2
Arise from seat	Independent	0
	Need assistance	1
The maximum walk distance(accompany with pain)	Unrestricted	0
	Restricted, > 1 km	1
	300 m ~ 1 km	2
	< 300 m	3
Daily Activities	Board standard airstairs	
	Independent	0
	Difficulty	1
	Unable	2
	Step down standard airstairs	
	Independent	0
	Difficulty	1
	Unable	2
	Squat or bend knees	
	Independent	0
	Difficulty	1
	Unable	2
	Walk over rough terrain	
	Independent	0
	Difficulty	1
	Unable	2

Therapeutic effect was assessed by comparing baseline and final conditions reported by the patient. Four categories were listed as below: clinical response-no symptom, normal function activity, clinical symptom score reduction ≥ 95%; markedly effective-no obvious symptom, normal joint function activity, able to participate in activity and work, clinical symptom score reduction 70 ~ 95%; improved-no pain, normal joints' flexion and extension, improvement in activity and work, clinical symptom score reduction 30 ~ 70%; ineffective-not arrived at the above standard involving with symptom and function impairment, clinical symptom score reduction < 30%.

This trial also records adverse effects reported by patients during treatment. The outcome measures above will be assessed before the treatment, the 30 days of the last moxibustion session and 6 months after the last moxibustion session.

### Design

A multi-centre (four centers in China), randomised, subject blinded(group A and B) and assessor blinded, positive controlled trial will be conducted at the Jiangxi Traditional Chinese Medicine Hospital in Nanchang, The first Affiliated Hospital with Anhui University of TCM in Hefei, Jiangsu Traditional Chinese Medicine Hospital in Nanjing, and Shanxi Traditional Chinese Medicine Hospital in Xian. The study will be sequentially conducted as follows: a run-in period of one week prior to randomisation, a treatment period of 30 days (5 sessions per week), and a follow-up period of six months. The total study period will be eight months. At the end of the run-in period, participants will be randomised to the heat-sensitive moxibustion group, the conventional moxibustion group, or the conventional drug treatment group by the central randomization system (Figure 1).This system is provided by China Academy of Chinese Medical Sciences, which adopted the computer telephone integration (CTI) technology to integrate computer, internet and telecom. The random number list will be assign by interactive voice response (IVR) and interactive web response (IWR)[26]. The success of blinding will be assessed at each participant's last visit. Researchers who did not participate in the treatment and who are blinded to the allocation results will perform the outcome assessment

**Figure 1 F1:**
[figure not shown]
**The flow diagram is intended to depict the passage of participants through this RCT**.

### Eligibility

#### Inclusion criteria

Eligible participants will be those previously diagnosed with moderate to severe KOA, according to the GPCRND-KOA criteria(> 5 score). Patients will be required to complete the baseline KOA diary. Written informed consent will be obtained from each participant. , Participants 38 ~ 70 years of age will be recruited from outpatient and inpatient in four centers. Standard of diagnosis listed as follows:(1) Keen pain almost occurred in the past one month; (2)Osteophyma at the edge of joints are all well demonstrated in X-ray; (3)Laboratory examinations of arthritis support the diagnosis of osteoarthritis;(4) Morning stiffness continued less than 30 minutes;(5) Bone sound existed when joints was taking flexion and/or extension. If a patient accord with (1), (2), or (1), (3), (4), (5), we can diagnose. Since the research involves moderate to severe KOA or severe KOA, the inclusion criteria will restrict the following conditions: According with the below KOA diagnosis standard, meanwhile, knee joints appear die Schwellung; Floating patella test is negative; Patients accept the treatment protocol in this trial; Acupoint heat-sensitization phenomenon exists in the region consisting of Yin Lingquan(SP9), Yang Lingquan(GB34), Liang Qiu(ST34), and Xue Hai (SP10).

Participants will be instructed to stop KOA symptomatic relief medication during the run-in and treatment periods and will be provided the usual care instruction for KOA.

#### Exclusion criteria

Participants will be excluded if they suffer from serious life-threatening disease, such as disease of the heart and brain blood vessels, liver, kidney and hematopoietic system, and psychotic patients. Participants will not be eligible if the female are in the duration of pregnancy or lactation. The following conditions are also excluded items: acute knee joint trauma or ulceration in its local skin; complicated with serious genu varus/valgue and flexion conttration.

### Treatment protocol

#### Heat-sensitive moxibustion

Moxibustion will be performed by certified acupuncture medical doctors at four centers. Qualified specialists of acupuncture in traditional Chinese medicine with at least five years of clinical experience will perform the acupuncture in this study. All treatment regimens will be standardized between four centers practitioners via video, hands-on training and internet workshops. Participants will be randomly assigned to the heat-sensitive moxibustion group, the conventional moxibustion group, or the conventional drug group. In the former groups, a 22 mm (diameter) × 160mm (length) moxa-sticks (Jiangxi Traditional Chinese Medicine Hospital, China) will be used. The patient is usually in the comfortable supine position for treatment, with 24°C ~ 30°C temperature in the room. He should be wearing loose trousers, especially making his knee joints exposed.

For the heat-sensitive moxibustion group, the moxa-sticks are lit by the therapist and held over the region consisting of Yin Lingquan(SP9), Yang Lingquan(GB34), Liang Qiu(ST34), and Xue Hai (SP10). The warming suspended moxibustion about distance of 3cm are used to search the acupoint heat-sensitization phenomenon. The following patients sensation will suggest the special heat-sensitization aupoint: diathermanous sensation due to moxa-heat, defining as the heat sensation conducting from the moxa local skin surface into deep tissue, or even into the joint cavity; expand heat sensation due to moxa-heat, defining as the heat sensation spreading the surrounding little by little around the moxa point; transfer heat sensation due to moxa-heat, defining as the heat sensation transferring along some pathway or direction, even to the ankle or hip conduction; non-heat sensation due to moxa-heat. When some acupoint exists one below sensation at least, the therapists mark the point as heat-sensitive acupoint. We try our best to seek all the special acupoints in each patient by the repeated manipulation.

The therapists begin to treat patients from the most heat-sensitive intensity acupoint. Treatment sessions end when patients are feel the acupoint heat-sensitization phenomenon disappeared. Generally speaking, we find the time range from 30 ~ 60 minutes.Patients receive the treatment two times/day in 1^st ^week(two times/day from 2^nd ^week ) for a total of 35 sessions over 30 days.

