#### Conventional moxibustion group

Patients assigning in conventional moxibustion group will receive fixed acupoint moxibustion. Common practices are similar with the first group. The different manipulation is that the therapists carry out warming moxibustion in traditional acupoint, selecting Xi Yan (EX-LE5) and He Ding (EX-LE2). One point is treated 15minutes a time. Three points are treated by suspended moxibustion at the same time. In the treatment, the therapists make patients the same intensity of local warm sensation as the former group. The sensation of acupoint heat-sensitization phenomenon is not pursued and not avoided in the treatment. Patients receive the treatment two times/day in 1^st ^week (two times/day from 2^nd ^week) for a total of 35 sessions over 30 days.

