
Among the changes, sensitized status is the common one, described that acupoints on the body surface may be sensitized with various types of sensitization. This sensitized acupoint is not only the pathological phenomenon reflecting the diseases but also stimulating location with acupuncture and moxibustion. Acupoint heat-sensitization is a type of acupoint sensitization, which derived from our clinical experience and research in past twenty years. The special acupoint makes accordance with the classical thought and theory from the Inner Canon of Huangdi.

Our empirical evidence engaged us to formulate the following hypothesis: selecting the heat-sensitized acupoint may obtain therapeutic effect far better than acupuncture and moxibustion at acupoints of routine rest state. The main aim of this trial is to test and verify the hypothesis. If we can confirm this hypothesis, promoting moxibustion clinical efficacy would be carried our in this extraordinary way. It is of great significance to develop the theory of acupuncture and moxibustion.

Therefore, the purpose of this trial is more than discuss the efficacy of moxibustion as treatment. The results of our trial will be helpful to supply the evidence on the rules of heat-sensitive moxibustion location in China.

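### Groups A and B differ in the rule that ends a session as well as in acupoint, so A versus B cannot verify the hypothesis that selecting the heat-sensitized acupoint produces the better effect

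*Protocol article*

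**What the plan says.** Under Treatment protocol, Heat-sensitive moxibustion, the therapist searches a region around four acupoints for heat-sensitized points and then treats them: "The therapists begin to treat patients from the most heat-sensitive intensity acupoint". The end of a session depends on the patient's sensation: "Treatment sessions end when patients are feel the acupoint heat-sensitization phenomenon disappeared". The usual length is given as an observed range: "Generally speaking, we find the time range from 30 ~ 60 minutes".

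Under Conventional moxibustion group, other practices are called similar to those of group A, and the contrast is introduced by acupoint: "The different manipulation is that the therapists carry out warming moxibustion in traditional acupoint". The timing follows: "One point is treated 15minutes a time. Three points are treated by suspended moxibustion at the same time". Intensity is aligned with group A: "the therapists make patients the same intensity of local warm sensation as the former group". The heat-sensitization sensation is neither sought nor avoided. Both moxibustion arms have 35 sessions over 30 days.

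On what the trial is to show, the Discussions section gives the hypothesis as "selecting the heat-sensitized acupoint may obtain therapeutic effect far better than acupuncture and moxibustion at acupoints of routine rest state" and calls testing it the main aim. The Discussion part of the abstract expects that "the result will clarify the rules of heat-sensitive moxibustion location", and the end of the Discussions section says much the same. The Objective, and the two questions posed in the Discussions section, are broader: they ask whether heat-sensitive moxibustion is better than conventional moxibustion.

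**The concern.** The hypothesis concerns one component of treatment, the choice of point. The two arms differ in at least two components: the choice of point, and the rule that decides when heating stops. Group A is dosed to a response and group B by the clock. Randomisation protects the comparison of A with B as whole regimens. It does not say which part of the regimen produced a difference.

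At stake is what may be concluded from a positive result. The protocol calls A versus B the question of greater interest and wants the result to guide practice. If a benefit is credited to point selection when treatment until the sensation fades contributed to it, practitioners could adopt the selection without the duration rule and not see the same effect.

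**Working it through.** The plan gives no figure on this point to reproduce. The check sets the two regimens side by side and then works out exposure.

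**Components by arm (Treatment protocol section)**

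| Component | Group A | Group B | Matched? |
|---|---|---|---|
| Points | heat-sensitized points found by search | fixed traditional points | no (intended contrast) |
| End of session | when the sensation disappears | after a fixed time | no |
| Session length | generally 30 to 60 min | 15 min, three points together | no |
| Intensity of local warmth | reference | same as A | yes |
| Sessions | 35 | 35 | yes |

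The search for points in A is part of selecting them and is not counted as a separate difference.

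**Elapsed time per session.** Ratio = A minutes / B minutes.
- Lower end: 30 / 15 = 2.0
- Upper end: 60 / 15 = 4.0

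**Elapsed time over the course.** Hours = 35 × minutes / 60.
- A: 35 × 30 / 60 = 17.5 h to 35 × 60 / 60 = 35 h
- B: 35 × 15 / 60 = 8.75 h
- A minus B: 17.5 − 8.75 = 8.75 h to 35 − 8.75 = 26.25 h

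**Point-minutes per session.** Point-minutes = points heated at once × minutes.
- B: 3 × 15 = 45
- A: 30 to 60. This assumes that points are treated one after another, which the instruction to begin with the most sensitive point suggests but does not state.
- Ratio A / B: 30 / 45 = 0.67 to 60 / 45 = 1.33

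The two measures disagree. On elapsed time A is clearly longer; on point-minutes B lies at the midpoint of A's range. The arithmetic therefore fixes neither the size nor the direction of a difference in total heat. What holds on either measure is that duration is response-driven in A and fixed in B.

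**Can the two components be separated?** That would need an arm with heat-sensitized points heated for a fixed time, or some way of matching duration between A and B. The third arm receives intra-articular injections and does not help. The Analysis section describes between-group comparisons with covariates only for baseline imbalance. Adjusting for session minutes would not solve the problem either: in A the minutes are set by the patient's response after randomisation, so they are not a legitimate baseline covariate.

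**The case against.** The best defence is that the stopping rule belongs to the concept under test. The Background section holds that an acupoint is defined by its state and not its position. On that view, treating a point while it is sensitized and stopping when it no longer is forms a single idea, and the rule could not be carried over to B, where sensitization is not sought. This has some force: where selection ends and dosing begins is partly a matter of judgement. But the hypothesis names selection. A theory of which point to choose does not say how long to heat it, and a heat-sensitized point could be heated for a fixed time. If the rule is inseparable from the treatment, the conclusion belongs to the whole treatment, which leads to the same correction.

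Several other objections stand and limit the point. A reader might infer:

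- **That the protocol hides the difference in duration.** It does not. The group B description goes on to give the 15 minutes and to say that the sensation is not pursued. What it does not do is present duration or the stopping rule as a difference from A.
- **That A receives more heat, or that duration explains a benefit as well as location does.** The documents support neither. Duration is a possible contributor of unknown weight.
- **That B's session may last 45 minutes.** The text says that the three points are treated together, which gives 15 elapsed minutes. Treating them in turn would run against that wording.
- **That every statement about location depends on A versus B.** The phrases on rules of location in the abstract and at the end of the Discussions section can also be read descriptively, as where heat-sensitized points are found and used. Only the hypothesis clearly needs the between-arm contrast.
- **That the trial's main comparison is invalid.** The Objective compares regimens, and the design answers that question.

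**Conclusion.** The point holds for the hypothesis and main aim in the Discussions section. A versus B can show that heat-sensitized points treated until the sensation disappears do better, or not, than fixed points heated for a fixed time. It cannot verify that the selection of the point is the reason, because the stopping rule also differs and nothing in the design or the stated analysis separates the two.

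The difference in stopping rule is certain from the text. The gap in elapsed time, a factor of 2 to 4, rests on the stated general range for A and on B's points being heated together. The point-minute ratio of 0.67 to 1.33 rests further on A's points being treated in sequence. No claim is made about the direction of any difference in total heat, or about how much of an effect the stopping rule would explain. The limit is on interpretation; randomisation and the regimen comparison are unaffected.

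**What to change.** 1. In the Discussions section, state the hypothesis and the conclusion to be drawn from it as a comparison of regimens: heat-sensitized points treated until the sensation disappears, against fixed points treated for a fixed time. This agrees with the Objective.
2. Limit the statements on rules of location, in the abstract and in the Discussions section, so that they do not attribute a difference between A and B to location alone. A descriptive account of where heat-sensitized points were found can stay.
3. In the Conventional moxibustion group section, say that session duration and the stopping rule differ from group A as well as the acupoints.

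These are changes of wording in three places. Neither regimen changes, and no arm or additional participants are needed. The cost is a narrower claim about location. A location-specific claim would need a design that matches duration and stopping rule between the arms.

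### The moxibustion schedule is internally inconsistent: neither the weekly nor the daily frequency stated for groups A and B gives the stated total of 35 sessions in 30 days

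*Protocol article*

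**What the plan says.** Three places in the protocol article fix the amount of moxibustion.

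- **Design:** "a treatment period of 30 days (5 sessions per week". No arm is named, but the injection group receives only five injections in total, so this weekly rate can only refer to the two moxibustion groups.
- **Heat-sensitive moxibustion (group A):** "two times/day in 1^st ^week(two times/day from 2^nd ^week", followed by a total "for a total of 35 sessions over 30 days".
- **Conventional moxibustion group (group B):** "two times/day in 1^st ^week (two times/day from 2^nd ^week", followed by the same total of 35 over 30 days.

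The Outcome section and the abstract time both post-baseline assessments by reference to the last moxibustion session. The Heat-sensitive moxibustion section also says that regimens will be standardised across the four centres by video, practical training and online workshops.

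**The concern.** The number of sessions is the dose of the experimental arm and of one of its two comparators. A weekly rate, a daily rate and a total over a fixed period should agree by simple multiplication, and these do not. The sentence in the two treatment sections also separates week 1 from later weeks, as if the frequency changed, and then repeats the same frequency. That suggests a slip in the text.

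Two things are at stake. First, a centre working from the Design sentence and a centre working from a treatment section could deliver different exposures. The Discussion asks whether moxibustion is superior to hyaluronate injection, and the answer depends directly on how much moxibustion was given. Second, the assessments are tied to the last session, so a different route to the last session shifts the time from randomisation to assessment.

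**Working it through.** **Inputs**

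- Treatment period: 30 days = 30/7 = 4.29 weeks (Design and both moxibustion sections).
- Weekly rate: 5 sessions (Design).
- Daily rate: 2 sessions in week 1 and 2 from week 2 (both moxibustion sections).
- Stated total: 35 sessions (both moxibustion sections).

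**Can the stated 35 be reproduced?**

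| Reading | Calculation | Sessions in 30 days |
|---|---|---|
| 5 sessions per week | 5 × 30/7 | 21.4 (20 to 22 by start day) |
| Twice daily, every day | 2 × 30 | 60 |
| Twice daily, with the Design sentence read as five treatment days a week | 2 × 5 × 30/7 | 42.9 (40 to 44 by start day) |
| Stated total | – | 35 |

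The first two rows are literal readings. The third is the most lenient way of combining the sections, and no section states it. None of the three gives 35.

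**Two cross-checks**

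- 35/(30/7) = 8.2 sessions per week, which is neither 5 nor the 10 to 14 that twice daily implies on five to seven days a week.
- 35/2 = 17.5 days. An odd total cannot be made up of complete two-session days.

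**Size of the gaps from the stated total**

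- 35/21.4 = 1.63.
- 60/35 = 1.71.

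**Effect on the timing of the last session, if a centre aims for 35**

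- Twice daily on every day: 17.5 days, so the last session falls on day 18.
- Five sessions per week: 35/5 = 7 weeks, which overruns the 30-day period.

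**Would correcting one frequency settle it?** As arithmetic only, 35 can arise if the rate differs between the first week and later: 7 × 2 + 21 × 1 = 35, or 5 × 2 + 25 × 1 = 35. The text states no such difference. Each of these patterns also has more than five sessions in every full week, so the Design sentence would still not fit. These sums are not a proposal for a schedule.

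**The case against.** The strongest reply is that this is a drafting slip in a condensed article. One wrongly repeated frequency could explain the conflict within the treatment sections. The total of 35 is written identically for both arms, practitioners are to be trained to a common regimen, and the full protocol held by the centres is not shown and may be consistent. All of that is fair, and it limits what can be claimed. It does not remove the contradiction: the same wording stands in two separate sections, nothing else in the article reconciles it, and training needs one schedule to train to.

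A reader might infer more than the document supports:

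- *That adherence has no denominator.* A total of 35 is written down for both arms. The article specifies intention-to-treat and states no adherence threshold or per-protocol analysis.
- *That centre-by-treatment effects will follow.* They are possible, but nothing shows that centres diverged. A centre that misread the schedule would be expected to misread it in both moxibustion arms, so an interaction in A versus B would need the A–B difference itself to depend on the number of sessions.
- *That A versus B is biased.* The schedule wording and total are the same in both arms, so the text itself favours neither.
- *That the dose is uncertain 2.8-fold (60/21.4).* This sets two extrapolations against each other and ignores the stated 35. The gaps from 35 are the fairer measure.
- *That the sample size is affected.* The number of sessions does not enter that calculation.

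**Conclusion.** The point holds as an internal inconsistency; it is not a criticism of a design choice. Five sessions per week (about 21), twice daily in both periods (60, or about 43 on five days a week) and a total of 35 in 30 days cannot all be true. The stated total differs from the two literal readings by about 1.6-fold and 1.7-fold.

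This rests only on the article's own figures and a 30-day treatment period; the start weekday does not change it. The consequences are possible, not demonstrated: different exposure between centres, bearing most directly on moxibustion versus injection, and different times from randomisation to assessment. Whether they arise depends on what the centres' own instructions say, which the article does not show.

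**What to change.** Reconcile the Design, Heat-sensitive moxibustion and Conventional moxibustion group sections to one frequency and one total that agree arithmetically over the stated treatment period. Keep the wording the same for groups A and B unless a difference is intended. If the frequency is meant to change after week 1, state both rates.

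Issue the reconciled schedule to all four centres, as a dated clarification if enrolment has begun. Record the sessions delivered and the date of the last session for each participant, so that exposure and assessment timing can be described by centre. Which schedule is right is for the clinical team, and this review takes no view on it.

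The cost is a text correction, a note to the four centres and two items on the data sheet if they are not already collected. The sample size and the stated analysis do not change.
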